# Mesalamine for Colorectal Cancer Prevention Programme in Lynch syndrome (MesaCAPP): a multicentre, multinational, randomised, two-arm, double-blind, phase II clinical study with mesalamine or placebo in carriers with Lynch syndrome – a study protocol

**DOI:** 10.1136/bmjopen-2025-100082

**Published:** 2025-11-09

**Keywords:** Clinical Protocols, Clinical trials, Gastrointestinal tumours, Endoscopy, Microbiota

## Abstract

**Introduction:**

Lynch syndrome (LS) carriers have a 20–46% lifetime risk of colorectal cancer (CRC) due to mismatch repair gene variants. Mesalamine (5-ASA, 5-aminosalicylic acid), used safely in patients with ulcerative colitis, may reduce CRC risk in LS by decreasing microsatellite instability, a key driver of LS-related cancer. This study evaluates 5-ASA’s efficacy as a tolerable chemopreventive drug, aiming to improve long-term CRC prevention in LS.

**Methods and analysis:**

This multicentre, multinational, randomised, double-blind, two-arm, phase II clinical study will compare the effects of a 2-year daily intake of 5-ASA (2000 mg) to placebo in LS carriers. The primary objective is to assess whether mesalamine reduces colorectal neoplasia, both benign and malignant, compared with placebo in LS carriers, as detected by colonoscopy at the end of the treatment period (24 months±1 month) and on study completion. Secondary objectives include evaluating whether 5-ASA reduces neoplasia/tumour multiplicity and progression compared with placebo at specified time points, examining variations in the effects of 5-ASA versus placebo based on cancer history, sex and age (<45 years vs ≥45 years), and assessing the safety of 5-ASA in LS carriers.

**Ethics and dissemination:**

The trial is currently open for enrolment, having received ethical approval from the Regional Ethical Review Board in Stockholm and funding from the Swedish Research Council. The study protocol is the finalised V.10.0 (11 April 2024), transitioned to the European Clinical Trials Information System. LS remains underdiagnosed, which may limit recruitment. The results are of global interest and will be published in peer-reviewed journals and presented at scientific conferences.

**Trial registration number:**

ClinicalTrials.gov: NCT04920149. EudraCT: 2019-003011-55. EU CT: 2024-514765-19-01.

STRENGTHS AND LIMITATIONS OF THIS STUDYA multicentre, randomised, double-blind, placebo-controlled, phase II trial with prospective surveillance delivers a rigorous framework and provides a unique opportunity to evaluate chemopreventive efficacy in LS.Genotype-defined LS carriers (*MLH1*, *MSH2/EPCAM* or *MSH6;* ACMG class 4/5), with genotype prespecified in analyses, that is, covariate/interaction, rather than as a randomisation stratum.Structured long-term follow-up with serial biospecimen collection enables high-resolution, exploratory, pharmacodynamic, microbiome and inflammatory biomarker analyses under harmonised standard operating procedures.Recruiting this rare, genotype-defined cohort across Nordic centres strengthens generalisability, with coordinated oversight—positioning the trial to deliver reliable, broadly applicable evidence.With n=150 and observed event rates, precision for modest effects and subgroup estimates is limited; however, the study retains robust power for the end of treatment primary analysis.

## Introduction

 Colorectal cancer (CRC) is the third leading cause of cancer-related deaths in both males and females.^1^ Lynch syndrome (LS) is characterised by deleterious variants in DNA mismatch repair (MMR) genes—*MLH1*, *MSH2*, *MSH6*, *PMS2* or *EPCAM*—carries a 20–46% lifetime risk of CRC, despite regular colonoscopy surveillance. The penetrance and variable expressivity of LS-associated gene variants exhibit variability.^2^ The prevalence of LS among patients with colorectal and endometrial cancer is approximately 1–4%. When extrapolated to the general population, the estimated prevalence of LS ranges from 1 in 2000 to 1 in 660, with higher estimates suggesting a prevalence as frequent as 1 in 279 individuals.^3^ This implies that up to 1.6 million individuals may be affected within the European Union.

Cancer prevention in LS has been previously studied, as chemoprevention represents a major hope for LS family members. The CaPP2 trial tested the effect of 600 mg of aspirin (acetylsalicylic acid, ASA) in a large multinational cohort, showing no benefit for its primary outcome.^4^ However, a secondary post-hoc analysis demonstrated a statistically significant delayed effect.^5^ Additionally, a study published in 2020 consolidated the findings of the prior study, further validating the earlier results.^6^ A limitation of this study cohort was the inclusion of patients without a verified variant in an MMR gene, potentially complicating data analysis and the interpretation of subsequent conclusions. Recognising the challenges of long-term tolerance to 600 mg of ASA and the potential efficacy of lower doses with comparable chemopreventive effects, the CaPP2 trial authors have initiated a follow-up study, CaPP3, to compare lower doses of ASA with 600 mg. However, even lower doses are associated with an increased risk of gastrointestinal ulcers and bleeding, presenting challenges for promoting long-term adherence across all age groups.

MMR germline mutations, combined with somatic inactivation of the second allele, impair the cell’s ability to repair mismatch errors during DNA replication. This can lead to cancer through the accumulation of mutations that inactivate tumour suppressor genes or activate oncogenes. Additionally, defective MMR impairs the correction of errors in small repetitive DNA sequences, known as microsatellites, resulting in microsatellite instability (MSI), a hallmark of defective MMR.^7^ A potential strategy to impede cancer development in LS is to enhance replication fidelity, thereby reducing the occurrence of MSI.^8^ In vitro studies have demonstrated that mesalamine (5-ASA), a well-tolerated drug used for over 30 years in the treatment of ulcerative colitis, can reduce MSI by improving replication fidelity. 5-ASA activates a replication checkpoint, providing additional time for cells to progress through the S-phase, thereby reducing replication errors.^9^ The effect of 5-ASA is specific to the position of the amino group,^10^ as neither 3-ASA nor 4-ASA exhibited this effect. This mechanism applies to various repetitive sequences, tetranucleotide, dinucleotide and mononucleotide repeats, such as those found in *TGFBR2* and *ACVR2*.^11 12^ In Msh2^loxP/loxP^ Villin-Cre mice, which closely mimic LS in the intestine, 5-ASA reduced tumour incidence, tumour multiplicity and the number of variants in five selected microsatellite repeats in normal mucosa.^13^ Notably, this chemopreventive effect was not observed with aspirin which does not influence MSI.^8 14^

Regular surveillance can reduce the cancer burden by enabling early detection when the disease is still in a curable stage. The study population undergoes routine colonoscopy with polypectomy at frequent intervals, starting at an early age in accordance with national guidelines. Complications from colonoscopies, particularly during polypectomy of small polyps in the right-sided colon, along with procedural discomfort, may affect patient compliance. Despite frequent surveillance, LS carriers have been shown to develop CRCs, although these are typically detected at earlier stages.^1^ Any intervention that reduces this burden could provide significant health benefits. 5-ASA, at the proposed dose, has been well tolerated in clinical trials^15 16^ and in routine clinical practice for over 30 years. In ulcerative colitis, long-term treatment with 5-ASA has been associated with a reduced risk of CRC.^17^ Effective chemoprevention is likely to require lifelong medication in otherwise healthy individuals. To ensure compliance and maximise the benefit-risk balance, chemopreventive drugs should have minimal short- or long-term adverse effects. 5-ASA appears to be an ideal candidate for LS carriers. This study has the potential to establish a new cancer-preventive treatment option for LS carriers, contributing to more individualised care.

## Methods and analysis

### Primary objective

The primary objective is to test whether 5-ASA reduces the occurrence of any colorectal neoplasia (both benign and malignant tumours) compared with placebo in LS carriers, as detected by any colonoscopy until the end of treatment (EOT) (24 months+3 months) and end of study.

### Secondary objectives

To evaluate whether 5-ASA reduces the number of colorectal neoplasms, including both benign and malignant tumours (tumour multiplicity), and prevents tumour progression compared with placebo in LS carriers at defined time points. Advanced adenomas are characterised by a diameter greater than 1 cm, villous or tubulovillous histology or high-grade dysplasia.To assess the safety profile of 5-ASA in LS carriers.To investigate metabolic, inflammatory and genomic biomarkers associated with LS and their relationship to 5-ASA treatment.

### Descriptive objectives

To describe tumour occurrence in the right colon, left colon and rectum, as well as the occurrence and location of serrated benign or malignant colorectal neoplasia, in the two treatment groups.To investigate whether differences between placebo and 5-ASA in the occurrence of colorectal neoplasia, tumour multiplicity and tumour progression are influenced by cancer history, sex or participant age (participants under 45 years vs 45 years and older).To describe the occurrence of colorectal neoplasia, tumour multiplicity and tumour progression for each sublocation in the colon and rectum.To determine whether the effects of 5-ASA differ between major LS genotypes.To evaluate the effects of 5-ASA treatment on the gut microbiota in LS carriers.To evaluate the effects of 5-ASA treatment on gut immunology and mucosal health in LS carriers.To assess compliance with 5-ASA treatment in LS carriers.

### Study design

This multicentre, multinational, randomised, double-blind, two-arm, phase II clinical trial will evaluate the efficacy of a daily intake of 5-ASA (2000 mg) compared with placebo in LS carriers over a 2-year treatment period (figure 1). 4 years after the treatment period, follow-up will include a phone consultation and a review of participants’ medical records. Cancer diagnoses and survival data will be collected for up to 18 years post-treatment. Eligibility screening will involve assessing 1000 participants, with 150 participants randomised in a 1:1 ratio into two groups (75 per group). Full registry entries (ClinicalTrials.gov, EudraCT and EU CT) are reproduced in online supplemental table 1. Eligible participants must be tumour-free carriers of an omitted pathogenic variant in a MMR gene, including those with a history of prior endoscopic polyp removal. Participants will be identified through local or national registries and collaborations with study sites. Tumour-free status will be confirmed using high-definition white-light colonoscopy (HDWL). Serum, plasma and stool samples will be collected, along with baseline and 24-month biopsies from normal tissue in the ascending colon, transverse colon and descending colon (figures2  3). Additional biopsies will be taken if polyps are detected.

**Figure 1 F1:**
[figure not shown]
Flowchart, MesaCAPP. ^1^EOT. cfDNA, cell-free DNA; EOT, end of treatment; MesaCAPP, mesalamine for Colorectal Cancer Prevention Programme in Lynch syndrome.

**Figure 2 F2:**
[figure not shown]
Visit and assessment schedule, MesaCAPP. ^1^After randomisation, ^2^Height will be measured only during the screening phase, ^3^ This is not applicable to participants in the non-treatment cfDNA group, ^4^If elevated, an additional test will be conducted within 1 week, ^5^Additional biopsies will be collected in the event of tumour detection, ^6^In accordance with national/local guidelines, ^7^Only at selected sites, ^8^If any malignancy is detected during the trial, an additional sample should be collected at the time of diagnosis, both before and after tumour excision, ^9^Samples are collected during each colonoscopy throughout the 6-year follow-up period, ^10^Colonoscopies are performed annually in years 3, 4, 5 and 6 after randomisation and the initial colonoscopy. Data from medical records are collected and entered into the eCRF. ALP, alkaline phosphatase; ALT, alanine aminotransferase; AST, aspartate aminotransferase; BMI, body mass index; BP, blood pressure; cfDNA, cell-free DNA; eCRF, electronic case report form; EoS, End of Study; IMP, investigational medicinal product; MesaCAPP, mesalamine for Colorectal Cancer Prevention Programme in Lynch syndrome; PR, pulse rate.

**Figure 3 F3:**
[figure not shown]
Microbiota sample collection, MesaCAPP. ^I^This is not applicable to participants in the non-treatment cfDNA group, ^II^The first 40 participants who consent to providing these additional samples (optional). cfDNA, cell-free DNA; MesaCAPP, mesalamine for Colorectal Cancer Prevention Programme in Lynch syndrome.

### Study assessment and procedures

The study includes a 1-month screening period, a 24-month intervention phase and a 4-year treatment-free follow-up. Participants’ medical records will be continuously monitored for up to 20 years following inclusion. Participants with pathogenic or likely pathogenic variants in defined MMR genes will be randomised to receive a once-daily dose of 5-ASA or a visually identical placebo. Eligible participants registered at the clinic will be informed of the study orally or in writing before their next routine visit, with details also available on a dedicated webpage. Following detailed verbal and written information given by the investigator, as well as signed consent, tumour-free LS carriers will be randomised to receive either the medication or placebo, along with a participant-diary. The informed consent form will be filed in the Investigator’s file, with a copy provided to the subject. Participants will attend site visits at 3 and 12 months postrandomisation for renal function assessment (blood creatinine), physical exams, vital signs, diary reviews and medication compliance. Site staff will also conduct phone calls every 6 weeks to monitor adverse events and adherence to the study drug or placebo, aiming for at least 75% compliance. During site visits, empty drug or placebo containers will be exchanged for new medication. An end-of-treatment visit is scheduled 24 months postrandomisation.

Annual or biennial HDWL-colonoscopies will be performed according to each participant’s surveillance protocol to detect colorectal neoplasia. Each procedure will document at least three landmark images (appendiceal orifice, caecum with ileocaecal valve and rectum with scope inversion). Standard quality metrics are recorded in accordance with routine care: the Boston Bowel Preparation Scale, withdrawal time and mandated landmark photographs are recorded.

A follow-up phone visit will occur 6 years after trial initiation to assess the long-term effects of the 2-year 5-ASA treatment. Non-interventional follow-up will continue through review of medical records up to 18 years post-treatment. Participants may withdraw from the study at any time. The sponsor reserves the right to terminate the study at any time. Analyses of gut immunology, microbiota, cell-free DNA (cfDNA) and other biomarkers will be performed using the best-available validated methods at the time of analysis, compared between treatment arms and adjusted for prespecified covariates. The cfDNA cohort is an exploratory substudy; it will not be analysed with respect to the primary endpoint of the parent study and will not contribute to that endpoint. Demographic and disease-related factors will be compared between the cfDNA subgroup and the full study population to assess representativeness.

### Primary endpoint

The occurrence of colorectal neoplasia (both benign and malignant tumours) in the two groups is presented as absolute frequencies and percentages, accompanied by 95% CIs. Logistic regression is used to assess differences in neoplasia occurrence between the active treatment and placebo groups, adjusted for country and prerandomisation cancer history. Treatment effects are expressed as ORs with corresponding 95% CIs.

### Secondary endpoint

The number of any colorectal neoplasia per participant will be compared between groups using analysis of variance, adjusted for country and cancer history before randomisation. If residuals do not meet normality assumptions, a suitable transformation will be applied to achieve normal distribution. Tumour progression across four ordered stages will be compared between groups using a χ² trend test, stratified by country and prerandomisation cancer history, and modelled with ordinal logistic regression. The dependence of treatment effects on CRC history, sex and participant age (<45 years and ≥45 years) will be assessed by modelling interactions between these variables and treatment in the relevant regression models. Safety data will be described and compared between groups in an exploratory analysis.

Extracolonic LS cancers and multiple primaries will be ascertained via medical records/registries, will not alter the primary endpoint and will be reported separately. Their inclusion as covariates will be limited to exploratory sensitivity analyses (prespecified in the statistical analysis plan, SAP), given their postrandomisation nature. Unless otherwise specified, the treatment-policy (intention-to-treat) estimand applies to the secondary endpoints.

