### Statistics, sample size calculation

The statistical design of this trial was originally informed by findings from the CaPP2 trial.^5^ CaPP2 was a 2-year study that employed a 2×2 factorial design to evaluate the effects of resistant starch and aspirin (ASA). After a mean of 27 months on the study drug, 18.9% of participants had developed neoplasia by the second endoscopy. Based on similar inclusion and exclusion criteria, it was estimated that 20% of the placebo group in this study would present with neoplasms after 24 months. A clinically meaningful outcome would be a reduction in neoplasia risk to 7.5%, similar to the reduction observed in the CaPP2 trial. Sample size calculations were based on an assumption of a 20% neoplasia rate in the control group. To detect a reduction to 7.5% in the experimental group (HR 0.375), with a two-sided significance level of 5% and 80% power, a sample size of 236 participants was estimated. At the first interim analysis of the ongoing MesaCAPP (mesalamine for Colorectal Cancer Prevention Programme in Lynch syndrome) study, a higher-than-expected overall neoplasia rate of 50% was observed. This change, while holding other factors constant, would increase the power to detect group differences from 80% to 99.9% with a sample size of 236 participants. A power of 80% would now be achieved with 131 participants. Under more conservative assumptions (HR 0.5) and an increased projected neoplasia rate of 65%, 80% power could still be reached with 101 participants. The trial plans to assess 1000 individuals for eligibility, with an estimated 50% agreeing to participate. However, approximately 75% of those screened are expected to fail to meet the inclusion criteria, based on data from the initial screening period. A 10% drop-out rate is anticipated and accounted for in the sample size calculation. Counts of neoplasia per participant will be analysed using Poisson or negative binomial regression, adjusted for country and prior CRC; overdispersion will be assessed and negative binomial used if indicated. All primary analyses are prespecified; sensitivity analyses assess robustness to missing primary endpoint data (details in the SAP).

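### Tumour multiplicity, a secondary endpoint, has two unreconciled analyses, and the normality rule attached to the ANOVA cannot be met when about half the counts are zero

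*Protocol article*

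**What the plan says.** Two sections of the protocol article specify the analysis of the number of neoplasms per participant.

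- **Secondary endpoint:** "The number of any colorectal neoplasia per participant will be compared between groups using analysis of variance", adjusted for country and pre-randomisation cancer history. The next sentence adds: "If residuals do not meet normality assumptions, a suitable transformation will be applied to achieve normal distribution". No transformation is named, and there is no fall-back if none succeeds.
- **Statistics, sample size calculation:** "Counts of neoplasia per participant will be analysed using Poisson or negative binomial regression, adjusted for country and prior CRC". The same sentence continues: "overdispersion will be assessed and negative binomial used if indicated". The test for overdispersion is not named.

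Neither section refers to the other, and neither ranks its method as main, sensitivity or replacement. Secondary objectives lists multiplicity together with tumour progression in one objective. On event rates, the statistics section reports that at the first interim analysis "a higher-than-expected overall neoplasia rate of 50% was observed", and it also considers a projected rate of 65%.

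**The concern.** The outcome, the unit and in effect the covariates are the same in both places, but the model families differ. One gives a difference in means, possibly on a transformed scale; the other gives a rate ratio. The two can reach different conclusions on the same data, and the text does not say which one counts.

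The ANOVA branch also promises something that these data cannot give. If about half the participants have no neoplasm, the raw residuals will fail any reasonable normality check. The rule will therefore always call for a transformation, chosen after looking at the residuals, and no candidate will meet its target. What remains is an open-ended search on a scale that is hard to interpret clinically.

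**Working it through.** **Plan's own figure.** The protocol gives no power or sample size for multiplicity. Its original total of 236 (20% v 7.5%, two-sided 5%, 80% power) does reproduce: the pooled-variance formula for two proportions gives 118 per arm. That figure concerns the yes/no endpoint and carries no assumption about counts.

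**Inputs from the protocol.** 150 randomised, 75 per arm; 10% drop-out, so 75 × 0.9 = 67.5, about 68 per arm; overall neoplasia rate 50% (interim, both arms together) or 65% (projection). The share of zero counts is therefore 1 − 0.50 = 50%, or 1 − 0.65 = 35%.

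**Inputs assumed.** The protocol gives no distribution for counts above zero. Counts are taken as gamma-Poisson with variance μ + kμ², where k is the dispersion (k = 0 is Poisson), and P(0) = (1 + kμ)^(−1/k). The simulations have no covariates.

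**Step 1: can a transformation give normality?** For any one-to-one function g, P(g(Y) = g(0)) = P(Y = 0). A point mass of 35% to 50% therefore survives every such transformation, whereas a normal variable has no point mass. Covariate adjustment does not remove it. With two arms, two countries (Sweden and Denmark) and two history groups, there are at most 2 × 2 × 2 = 8 fitted values, so about 0.5 × 150 = 75 zeros fall on at most eight residual values.

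This was checked by simulation with 75 per arm, 35%, 50% or 65% zeros, k = 0, 1 or 2, and 400 trials in each of the nine settings. Shapiro-Wilk rejected normality in 100% of trials for raw counts, log(1+y), square root, Anscombe, Box-Cox and rank-based inverse normal scores.

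**Step 2: does that damage the ANOVA test?** No. In those nine settings its null rejection rate was 2.5% to 7.3% across all scales, with a Monte Carlo error of √(0.05 × 0.95/400) = 1.1 points.

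**Step 3: what does the choice of method cost?** Setting: 68 per arm, control mean 1.2, 1,500 trials. The control-arm share of zeros is 1/2.2 = 45% at k = 1 and 3.4^(−1/2) = 54% at k = 2.

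| | ANOVA, raw | ANOVA, log(1+y) | Negative binomial |
|---|---|---|---|
| Null rejection, k = 1 | 5.9% | 5.5% | 5.8% |
| Null rejection, k = 2 | 5.4% | 4.5% | 5.8% |
| Power, rate ratio 0.5, k = 1 | 74.7% | 72.7% | 76.4% |
| Power, rate ratio 0.5, k = 2 | 57.1% | 52.8% | 59.7% |

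Loss against negative binomial:

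- Raw counts: 76.4 − 74.7 = 1.7 points and 59.7 − 57.1 = 2.6 points.
- Log(1+y): 76.4 − 72.7 = 3.7 points and 59.7 − 52.8 = 6.9 points.

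At k = 0 (2,000 trials) there is practically no loss: 96.1% raw, 95.0% log, 95.6% negative binomial. Across repeated runs at k = 0.5 to 2, the loss was up to about 4 points for raw counts and about 3 to 7 points for log(1+y).

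**Step 4: how often do the two methods disagree?** In the 68-per-arm setting, log ANOVA and negative binomial fell on opposite sides of 5% in roughly 3% to 13% of trials. In a second set (75 per arm, rate ratio 0.6, baseline mean giving 50% zeros, 400 trials), disagreement was 4%, 11% and 14% at k = 0, 1 and 2. Power in that set was 46% v 55% at k = 1 and 42% v 50% at k = 2 (log ANOVA v negative binomial).

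**Step 5: is the count-model branch sound as written?** The two-stage rule was simulated with a 5% likelihood-ratio test for overdispersion (an assumption, since the protocol names none). At k = 1 and 2 the test detected overdispersion in 99.95% and 100% of null trials. Type I error was 6.4% and 4.6%, the same as always using negative binomial. At k = 0, 0.25 and 0.5 it was 4.8%, 5.6% and 5.4%. Power matched negative binomial within 0.5 points.

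**The case against.** The strongest defence is that little statistical damage follows. The ANOVA holds its type I error, the power loss is a few points and depends on an assumed dispersion, the primary endpoint is untouched, and a statistical analysis plan that is not shown may already say which method is main. All of this stands as a limit on the size of the point. It does not remove the point, because the article does more than leave a detail to another document: it states two different analyses for one endpoint.

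A reader might infer that the Poisson route would greatly inflate false positives. Plain Poisson did reject in 19% (k = 1) and 28% (k = 2) of null trials. The documents do not support that inference. The plan switches to negative binomial when overdispersion is indicated, and step 5 shows that this rule behaves like negative binomial from the start. Nor do they say that counts are overdispersed, since they give no count distribution.

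A reader might also infer that the ANOVA is invalid because its residuals are not normal. Step 2 shows otherwise: the rule fails, not the test.

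**Conclusion.** The point holds as an inconsistency on a secondary endpoint, together with a rule that cannot be carried out. The contradiction rests on the text alone. The failure of the normality rule rests on the protocol's own 50% rate and is unchanged at 65%.

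The consequences are moderate: a choice between methods left open in the text, an effect that is not a rate ratio, and, if counts are overdispersed, the power losses and conflicting verdicts given in steps 3 and 4. Those sizes depend on assumed dispersion, means and rate ratios. With no overdispersion the power loss is practically nil.

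Multiplicity should not be read as the leading secondary endpoint, because the protocol sets no hierarchy. Nor do the documents show that the choice will in fact be made after the data are seen; they show only that this text does not prevent it.

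**What to change.** 1. In Secondary endpoint, delete the ANOVA and transformation sentences for multiplicity, or label them a sensitivity analysis with one named scale and no normality condition.
2. Name the count model as the single main analysis in both sections, for example negative binomial regression adjusted for country and prior CRC, reported as a rate ratio with 95% CI. Use one term for the history covariate throughout.
3. The overdispersion check may stay, provided that its test and threshold are stated. Negative binomial from the start is equally acceptable.

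No change to the covariate set and no follow-up offset is needed to resolve this point.

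The cost is wording only: the method is already in the protocol, and the sample size does not change. End of treatment for the last participant is scheduled for Q3 2027, so the change can still be made and dated before database lock, without sight of counts by arm.
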